# An evaluation of the effectiveness of a multi-modal intervention in frail and pre-frail older people with type 2 diabetes - the MID-Frail study: study protocol for a randomised controlled trial

**DOI:** 10.1186/1745-6215-15-34

**Published:** 2014-01-24

**Keywords:** Multi-modal intervention, Frail, Pre-frail, Type 2 diabetes

## Abstract

**Background:**

Diabetes, a highly prevalent, chronic disease, is associated with increasing frailty and functional decline in older people, with concomitant personal, social, and public health implications. We describe the rationale and methods of the multi-modal intervention in diabetes in frailty (MID-Frail) study.

**Methods/Design:**

The MID-Frail study is an open, randomised, multicentre study, with random allocation by clusters (each trial site) to a usual care group or an intervention group. A total of 1,718 subjects will be randomised with each site enrolling on average 14 or 15 subjects. The primary objective of the study is to evaluate, in comparison with usual clinical practice, the effectiveness of a multi-modal intervention (specific clinical targets, education, diet, and resistance training exercise) in frail and pre-frail subjects aged ≥70 years with type 2 diabetes in terms of the difference in function 2 years post-randomisation. Difference in function will be measured by changes in a summary ordinal score on the short physical performance battery (SPPB) of at least one point. Secondary outcomes include daily activities, economic evaluation, and quality of life.

**Discussion:**

The MID-Frail study will provide evidence on the clinical, functional, social, and economic impact of a multi-modal approach in frail and pre-frail older people with type 2 diabetes.

**Trial registration:**

ClinicalTrials.gov: NCT01654341.

## Background

Diabetes has a high prevalence in ageing populations, affecting approximately 20% of people aged 70 years or over. It is anticipated that by 2050 the number of cases of diabetes will have increased by fourfold in people older than 70 years [1]. Diabetes is associated with increasing frailty and functional decline in older people [2]. Frailty is defined as a clinical syndrome in which three or more of the following criteria are present: unintentional weight loss (≥4.5 kg in past year), self-reported exhaustion, weakness (grip strength), slow walking speed, and low physical activity [3].

Diabetes has serious personal and social consequences, and is a significant public health burden in terms of rising health care costs; in Spain, annual direct health care costs have been estimated at 2.5 billion euros [4]. In recent studies of older people, up to 28% of those with diabetes required some help with activities of daily living, compared with 16% of those without the condition [5]. This functional decline can be explained in only half of the cases by the classical complications of the disease, such as coronary artery disease, stroke, and peripheral vascular disease [5]. The worsening in functional status due to deterioration of skeletal muscle, increased co-morbidities, and adverse effects of overmedication associated with diabetes, results in many older frail people becoming more disabled, with an impaired quality of life associated with increased use of health care resources [6-8].

There is a marked lack of intervention studies that aim to reduce functional decline and improve quality of life in older people with diabetes and until relatively recently, most of the clinical guidelines for treating type 2 diabetes were of limited use in these subjects. A focus on improvements in function and well-being may be fundamentally of more clinical benefit in older frail people with diabetes than attention to metabolic control alone [9]. In older adults and frail individuals, resistance training is now considered to be an important component of diabetes management and prevention, mainly through increasing muscle mass, strength, and power [10]. This leads, in turn, to increased mobility and a decreased risk of falling [11]. In addition, resistance training has been proven to improve insulin sensitivity and fasting glycaemia, and to decrease abdominal fat in older people with type 2 diabetes [10]. It has been previously shown that intensive glucose lowering therapy (targeting a glycated haemoglobin level below 6.0%) in patients with type 2 diabetes was associated with a reduction in 5-year non-fatal myocardial infarction but increased 5-year mortality [12,13]. More recently, it was reported that an intensive lifestyle intervention focusing on weight loss in overweight or obese adults with type 2 diabetes led to improvements in glycaemic control, blood pressure, high-density lipoprotein (HDL)-cholesterol, and triglycerides [14]. However, the intervention failed to reduce the incidence of cardiovascular events [15]. These observations provide sufficient motivation for evaluating non-metabolic control as an alternative (and complementary) way of improving clinical outcome.

The long-term impact of diabetes in an ageing population results in substantial health care expenditure. This further emphasises the potential value of an intervention that can prevent or delay the onset of diabetes-associated frailty. The multi-modal intervention in diabetes in frailty (MID-Frail) study focuses on the use of interventions designed to improve functional status and enhance quality of life by acting on the mechanisms involved in frailty and its progression to adverse outcomes [16]. The MID-Frail study brings together 16 partners from seven countries in the European Union (EU) and will run for 4 years, with the intervention lasting 2 years. The primary objective of the MID-Frail study is to evaluate, in comparison with usual clinical practice, the effectiveness of a multi-modal intervention (specific clinical targets, education, diet, and exercise) in frail and pre-frail subjects aged ≥70 years with type 2 diabetes in terms of the difference in function 2 years post-randomisation. Difference in function will be measured by changes in summary ordinal score on the short physical performance battery (SPPB) of at least one point.

## Methods/design

### Subjects

#### Inclusion criteria

Subjects are eligible to enter the study if all of the following apply:

1) The subject is willing and able to give written informed consent for participation in the study.

2) The subject is aged 70 years or older, with a diagnosis of type 2 diabetes for at least 2 years.

3) The subject fulfils the Fried’s criteria for frail or pre-frail individuals (Table 1).

4) The caregiver has agreed to participate in the study and to give informed consent for participation in the carer burden part of the study. If the caregiver does not agree, the subject may continue to participate in the study, but information about caregiver burden will not be collected.

**Table 1 T1:** Fried’s criteria for study inclusion

**Criterion**	**Definition**
1. Weight loss	Unintentional weight loss of 4.5 kg during the past year
2. Exhaustion	Using the responses (yes/no) to two statements on the CES-D scale
3. Physical activity	Is the weekly physical activity of the subject lower or equal to (yes/no): men: <383 kcal per week (walking: <2.5 hours per week) women: <270 kcal per week (walking <2 hours per week)
4. Slowness	Assessed by walk time and stratified by gender and height
5. Weakness	Assessed by grip strength and stratified by gender and BMI

Frailty is indicated by satisfying three or more of the criteria; pre-frailty is indicated by satisfying one or two of the criteria [3]. BMI, body mass index; CES-D, Center for Epidemiologic Studies Depression.

Fried’s criteria for frailty were chosen as they are easy to implement and allow the selection of subjects who are not dependent (moderately or highly). In addition, these criteria should avoid selection bias and prevent the enrolment of a high percentage of subjects with disabilities at baseline.

#### Exclusion criteria

Subjects cannot enter the study if any of the following apply:

**Figure 1 F1:**
[figure not shown]
**The short physical performance battery (SPPB)****[**[21]**].** Reprinted from Journal of Biomechanics, Vol. 45, Riskowski JL, Hagedorn TJ, Dufour AB and Hannan MT, Functional foot symmetry and its relation to lower extremity physical performance in older adults: the Framingham Foot Study, pp. 1796–1802, Copyright 2012, with permission from Elsevier.

1) Barthel score lower than 60 points [17].

2) Inability to complete the SPPB (total score = 0) (Figure 1) [18].

3) Mini Mental State Examination (MMSE) score of less than 20 points [19].

4) Subject is unwilling or unable to consent or unable to participate safely in the intervention programme.

5) Previous history of myocardial infarction within 6 months, unstable angina, or congestive heart failure at stage III to IV of the New York Heart Association (NYHA) classification [20].

6) The subject is clinically unstable in the clinical judgment of the investigator.

7) Terminal illness (life expectancy <6 months).

8) Any other condition that, in the clinical judgment of the investigator, means that it would not be in the subject’s best interests to enter the study.

9) Concurrent participation in a clinical trial or any other investigational study.

To date, the study has been approved by 16 institutional ethics committees in Spain (see further details in Additional file 1). The study will be carried out in accordance with Good Clinical Practice, applicable local regulatory requirements, and the guiding principles of the Declaration of Helsinki.

### Study design

This is an open, randomised, multicentre study, with random allocation by clusters (each trial site) to a usual care group or an intervention group (Figure 2). Each site will enroll on average 14 or 15 subjects. National research centres in Belgium, Czech Republic, Italy, and Germany (one each) and in France, United Kingdom, and Spain (two each) will each be responsible for 11 or 12 sites. Each site will be monitored to ensure full adherence to the study protocol and the integrity of the data collected. An adaptive monitoring strategy has been adopted in which some sites will be monitored remotely. The study will evaluate the intervention through the difference in functioning between intervention and usual care groups; an economic evaluation of the intervention and of quality of life will also be carried out.

**Figure 2 F2:**
[figure not shown]
Detailed study flowchart.

#### Randomisation

Before randomisation, each trial site will identify and make a list of 50 to 75 potential subjects. Identifying individuals for recruitment before randomisation will help to avoid subject selection bias [22]. Once this list is complete, the investigator will have 1 month to obtain signed informed consent from at least seven subjects (roughly half of the site target size) on that list. Then, the site will be randomised and exercise machines delivered. Randomisation will be performed centrally by onmedic (Barcelona, Spain) in collaboration with Cardiff University (Cardiff, UK).

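### Sites are randomised once about half their subjects have consented, so up to about half of this open cluster trial may be recruited with the arm known, and the pre-randomisation list protects only in part

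*Protocol article*

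**What the plan says.** The Protocol article, Randomisation section, fixes a sequence. Before randomisation, "each trial site will identify and make a list of 50 to 75 potential subjects". The investigator then has one month "to obtain signed informed consent from at least seven subjects (roughly half of the site target size) on that list". The next step is: "Then, the site will be randomised and exercise machines delivered". The stated purpose of the list is that "Identifying individuals for recruitment before randomisation will help to avoid subject selection bias".

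The Study design section describes an open trial in which the trial site is the unit of allocation. It adds: "Each site will enroll on average 14 or 15 subjects". It names ten national centres (one each in four countries, two each in three) that "will each be responsible for 11 or 12 sites".

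Several exclusion criteria depend on judgment. Criterion 4 covers, among others, subjects who could not take part safely in the programme. Criterion 6 covers clinical instability as the investigator sees it. Criterion 8 is a catch-all that lets the investigator exclude anyone whose interests entry would not, in their view, serve.

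The Statistical analysis section plans a hierarchical logistic model by intention to treat. It controls for baseline function and for subject characteristics, with age, gender and comorbidities as examples.

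**The concern.** In a cluster trial, randomising sites protects the comparison of subjects only if subjects enter without regard to their site's arm. Here the trigger for allocation is a consent count that the article itself describes as about half the site target. The rest can then be enrolled by people who know the arm, and at intervention sites with the training machines due or already in place.

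Three routes to imbalance stay open even if every late recruit comes from the list:

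- The investigator chooses whom to approach next.
- The exclusion for those who could not safely take part has practical consequences at an intervention site and few at a usual-care site. It may therefore be applied differently by arm, even in good faith.
- Subjects may accept or refuse according to what they are offered.

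Intention-to-treat analysis does not correct who entered each arm. Regression on baseline function, age, gender and comorbidities removes measured differences but not those in motivation or readiness to train. If the two sets of late recruits differ in their 2-year risk of functional impairment, part of the observed difference is not an effect of the programme.

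**Working it through.** **1. Reproduce the plan's own figure (Power and sample size section).** Inputs: 30% yearly incidence, effect size 20%, two-sided α 0.05, power 0.8, intra-cluster correlation 0.05, mean cluster size 15, coefficient of variation 0.25, 20% loss.

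- Control risk: 1 − 0.7² = 0.51. Intervention risk with the 20% read as relative: 0.8 × 0.51 = 0.408. Difference: 10.2 points.
- Two-proportion formula with continuity correction: 393 per arm.
- Design effect: 1 + ((1 + 0.25²) × 15 − 1) × 0.05 = 1.7469. 393 × 1.7469 = 686.5.
- 686.5 / 0.8 = 858.2, rounded up to 859 per arm, 1,718 in total. This matches the article, so the sample size is not in question and the relative reading of the 20% is supported.

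**2. Share recruited after allocation.** Inputs: minimum of 7 consents, 14 or 15 subjects per site. Share = 1 − 7/site size.

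- 14 per site: 7/14 = 50%. 15 per site: 8/15 = 53%.
- In total: 0.50 × 1,718 = 859; 0.533 × 1,718 = 916.
- From the site count (10 centres × 11 or 12 = 110 to 120): 1,718 − 7 × 120 = 878 (51%); 1,718 − 7 × 110 = 948 (55%). The last figure implies 1,718/110 = 15.6 subjects per site, slightly above the stated average.

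These are upper bounds, because seven is a minimum. A site with 10 consents before allocation would have 4/14 to 5/15 exposed (29-33%). A site with all 14 or 15 would have none.

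**3. What the list restricts.** A list of 50 to 75 for 14 or 15 places holds 50/15 = 3.3 to 75/14 = 5.4 names per place. Subtracting only the seven consenters leaves 43 to 68 names, but that ignores people already approached who refused or proved ineligible. Assume the list was sized to its expected yield. Seven consents then use 7 × 50/15 = 23 to 7 × 75/14 = 37.5 names. About 25 to 40 remain for 7 or 8 places, and most of those would not yield a subject.

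**4. Hypothetical effect on the primary comparison.** The selection effect X is an assumption; no figure for it is in the article. Suppose there is no true effect and late recruits in the two arms differ by X in 2-year risk. Bias b = share × X. Evaluable per arm: 0.8 × 859 = 687. Effective number: 687.2/1.7469 = 393. Standard error = √[(0.51 × 0.49 + p(1 − p))/393], with p = 0.51 − b. Type I error = 1 − Φ(1.96 − b/SE) + Φ(−1.96 − b/SE).

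| X (assumed) | b at 50% share | b / 10.2 | Type I error at 50% | at 53.3% |
|---|---|---|---|---|
| 5 points | 2.5 points | 0.25 | 11% | 12% |
| 10 points | 5.0 points | 0.49 | 29% | 32% |
| 15 points | 7.5 points | 0.74 | 56% | 62% |

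This is an unadjusted two-proportion calculation at maximum exposure.

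**The case against.** The strongest reply is that the article claims only that listing candidates helps against selection bias, and it does help. If later recruits must come from the list, the pool was fixed blind to arm, and those who consented before allocation are protected. A reader might infer that the safeguard is defeated altogether. The text does not support that; the protection is partial. Nor do the late recruits drive the primary comparison: nothing gives them extra weight, and they make up at most about half of it.

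Other points also stand:

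- Exposure of half is a ceiling, not an estimate, and investigators would not have a free choice among 43 to 68 names.
- A reader might infer that baseline SPPB is measured with the arm known. The article does not say when it is measured. SPPB is also an eligibility test, and the study flowchart is not shown, so no finding can rest on this.
- The type I error figures are not a property of this trial. The selection effects are assumed, the planned model would remove the measured part, and the direction is not given. The endpoint is a change in SPPB, so fitter recruits need not have lower event risk.
- The full protocol may specify the order of approach, and an unseen analysis plan may contain a sensitivity analysis. Their absence from an article is not the defect.

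What the reply does not answer is the published sequence itself. A pre-made list does not stop arm-dependent choice, exclusion or refusal among those still on it.

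**Conclusion.** The point holds as one about a badly fixed rule. Randomising a site at seven consents in an open cluster trial leaves up to 50-53% of an average site's subjects, at most roughly 860-950 of 1,718, open to selection and consent with the arm known. That late recruitment happens is inferred from the description of seven as about half the target; the phrase has no other natural reading. The ceiling assumes every site stops at the minimum.

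The size of any resulting bias cannot be determined from the document. The 2.5, 5 and 7.5-point spurious differences, with type I errors of about 11%, 29% and 56%, only show what assumed selection effects of 5, 10 and 15 points would do before adjustment. They do not show that such effects will occur. The comparison with 10.2 points rests on reading the 20% effect as relative, which reproduces the stated sample size.

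**What to change.** Where feasible, obtain consent and confirm eligibility for the full site target of 14 or 15 before the allocation is disclosed. Late exposure at those sites falls to zero, and 1,718 is unchanged because no power input moves. The cost is a possible delay of some weeks at some sites, during which subjects who have already consented wait.

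Where a site cannot do this:

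- Approach the remaining listed subjects strictly in a random order generated centrally before allocation.
- Log every approach, refusal and exclusion, with the reason, and report them by arm.
- Record each consent date relative to the date the site's allocation was disclosed.
- Add a sensitivity analysis of the primary endpoint in subjects who consented before allocation.

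The order and the log cost little. The restricted analysis is less precise, though not in proportion to the subjects lost, because clusters of seven carry a smaller design effect: 1 + ((1 + 0.25²) × 7 − 1) × 0.05 = 1.32, assuming the same coefficient of variation and intra-cluster correlation. With half the subjects the effective number per arm is 343.6/1.32 = 260 against 393, so the standard error rises by a factor of √(393/260) = 1.23.

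The Trial status section says the trial is still being set up, so the change can be made now. The order and timing of consent cannot be repaired after recruitment.

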#### Intervention group

The study intervention consists of a multi-modal programme comprising glycaemia and blood pressure monitoring to reach pre-defined targets, a 16-week resistance exercise programme based on leg press and leg extension exercises (Additional file 2), and a nutritional and educational programme. The exercise and the nutritional and educational programmes will be run at the study site at the beginning of year 1 and repeated at the beginning of year 2. All subjects in this intervention group will follow the multi-modal programme.

##### Glycaemia and blood pressure monitoring

The targets for glycaemia and blood pressure control will be pre-defined; however, the treatment required to achieve them will not be pre-defined. Treatment protocols at each site will be used to ensure that target values are reached within 6 months of enrolment. There will be no target for cholesterol or its fractions and there are no specific recommendations for the use of aspirin. The target for glycaemia will be: optimal glycated haemoglobin in the range of 7 to 8% (53 to 64 mmol/mol); the target for blood pressure will be <150/90 mmHg.

##### Exercise programme

Subjects will undergo 2 weeks of pre-training assessment before the exercise programme begins. They will be familiarised with the exercises through several submaximal and maximal performances, using one-repetition maximum (1RM), and baseline measurements will be taken. In all tests of exercise performance, subjects will be encouraged verbally to perform each test action as forcefully and as rapidly as possible.

##### Exercise methodology

The exercise programme used in the MID-Frail study will be similar to one described previously [10,23]. The subjects will be asked to report to the training facility on 2 days each week; each session will last from 20 to 30 minutes. Training sessions will be separated by a minimum of 2 days. Subjects will undertake supervised resistance exercise for 16 weeks starting at week 2 (baseline) and the assessments carried out at baseline will be repeated in week 6, week 10, and week 18. Each training session will include two exercises for the leg extensor and knee extensor muscles. Only resistance machines will be used throughout the training period (Exercycle, Exercycle S.L., Alava, Spain). For the first 8 weeks of the training period, subjects will train with loads of 40 to 60% of the individual 1RM, 8 to 12 repetitions per set, and 2 to 3 sets. For the last 8 weeks of the training period, the loads will be 70 to 80% of the maximum, 4 to 6 repetitions per set (higher loads), and 3 to 4 sets.

##### Nutritional and educational programme

The MID-Frail nutritional and educational programme is aimed specifically at older people with diabetes and is derived from a published programme for this particular population [24]. The programme consists of sessions that aim to increase the subject’s knowledge and understanding of diabetes, to develop practical skills in diabetes self-management, and to enhance the likelihood of improved and safe control of glycaemia [25].

Each subject will undergo pre-trial assessment of nutritional status and any requirement for weight reduction or weight gain and the need for diet modification. Thereafter, the intervention consists of clinician-moderated sessions in a clinic or general practitioner surgery with small groups of four to eight subjects. Seven separate 45-minute sessions will be delivered, with two each week for 3 to 4 weeks; the sessions will be held on the same day as the exercise sessions.

#### Usual care group

Subjects in the usual care group will receive the routine care a subject with diabetes would normally be expected to receive from his/her local health care system, including his/her general practitioner.

